### Cost-Effectiveness and Utility Measures

A societal perspective will be taken as the basis for the cost-effectiveness measurement and analyses. Thus, direct health care costs, direct non-health care costs, and indirect costs will be used as the economic indicators[54,55]. These cost measures are collected from standardized study provider forms at each study treatment visit and patient self-report questionnaires at months 4, 12, 26, and 52. Telephone interviews occur monthly from weeks 12 to 52.

Direct costs for each patient will represent the pain- or disease-related medical costs based on utilization and estimated costs. This will include the costs of the study treatments to which patients are randomized and costs for additional visits to non-study health care providers, prescription medications, advanced imaging (CT, MRI), and hospitalization. Direct non-health care costs will include out-of-pocket expenses (non-prescription medications), informal care, and travel expenses.

Indirect costs will include loss of productivity due to back-related absence from work or days of inactivity. Days in which activity is restricted due to LBP are assessed by three questions based on items from the National Health Interview Survey (NHIS)[45].

Cost utility will be measured using the EuroQol 5D, which has been valued by a large sample of the general population using time trade-off evaluations. It is a brief, easily completed instrument and is considered to be one of the best preference-based measures currently available[41,56].

### Other Measures

Patient expectations are evaluated based on questions used in previous studies by the investigators. Prior to randomization (at BL2), patients are asked to rate how helpful they believe each treatment to be on an 11-box scale (0 = not at all helpful, 10 = extremely helpful)[57].

Patients are asked to report side-effects in the patient self-report questionnaires by choosing from a list of side-effects generated from previous studies by the investigators assessing chiropractic care and exercise[58,59]. For each side-effect chosen, the patient is asked to rate the bothersomeness of the side-effect on an 11-box scale (0 = not at all bothersome, 10 = extremely bothersome). This method of recording side-effects is an attempt to standardize side-effect reporting in clinical trials, which has been inadequately addressed in much of the research performed to date[9].

## Data Analysis

### Treatment Effectiveness

Power was calculated to detect an 8 to 9 percentage point difference between groups in the primary outcome measure of patient self-reported pain after 12 weeks and one year. A sample size of 100 patients per group provides 80% power assuming an alpha level of .05. This allows for a 15% loss to follow up.

Mixed-Model analysis of covariance (ANCOVA) will be used to test for differences between groups in patient-rated primary and secondary outcomes in both the short- (12 weeks) and long-term (52 weeks). Baseline values will be used as covariates when appropriate; intention-to-treat analysis will be used[60]. A sensitivity analysis will be performed, including patient expectations as a covariate to assess its influence on study results.

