### Primary Aim

The primary aim of the study is to determine the relative clinical efficacy of 1) **monodisciplinary, chiropractic care **and 2) **multidisciplinary, integrative care **for LBP of greater than 6 weeks duration, in both the short-term (after 12 weeks) and long-term (after 52 weeks). Patient-rated back pain is the primary outcome measure.

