### Self-report outcome measures

**Patient-rated pain **is the primary outcome measure. Patients are asked to rate their typical LBP over the last week on an ordinal 11-box scale (0 = no LBP, 10 = the worst LBP possible)[35].

Secondary outcome measures include frequency of symptoms, low back disability, fear avoidance, self-efficacy, general health status, improvement, satisfaction, work loss, and medication use.

**Frequency of symptoms **is rated for 1) back pain, 2) leg pain, 3) numbness or tingling in the leg, foot or groin, and 4) weakness in leg or foot on a 0 to 6 scale (0 = not at all, 6 = always)[36,37].

**Low back disability **is measured with the Modified Roland Scale, a 23-item questionnaire that assesses the degree to which LBP restricts daily activities[36,38].

**Fear avoidance **is evaluated with the Fear-Avoidance Beliefs Questionnaire, consisting of 21 items that quantify fear-avoidance beliefs about work and physical activity. Each item is a statement; the patient is asked to rate their degree of agreement/disagreement on a 0 to 6 scale (0 = completely disagree, 6 = completely agree)[39].

**Self-efficacy **is measured by the Pain Self-Efficacy Questionnaire, a 10-item scale used to assess the level of self-confidence in performing functional and social activities despite the presence of pain. Scores range between 0 (no self-efficacy) and 60 (highest self-efficacy)[40].

**General health status **is assessed by the EuroQol 5D, a multi-attribute utility scale (MAUS) covering five dimensions (mobility, self-care, usual activities, pain/discomfort, and anxiety/depression) with three levels (no problem, moderate problem, severe problem)[41,42].

**Improvement **is measured by asking patients to compare their LBP condition to what it was before treatment using a 9-point ordinal scale. Response choices range from no symptoms (100% improvement) to twice as bad (100% worse)[43].

**Satisfaction **is assessed using seven questions addressing different aspects of patient care with 5 response choices (1 = poor, 5 = excellent)[32,44]. Overall satisfaction with care is also measured on a 7-point ordinal scale (1 = completely satisfied, 7 = completely dissatisfied).

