### Cost-effectiveness Analysis

A cost comparison of the intervention groups using data on direct and indirect costs will be conducted. Cost differences between groups will be estimated for all costs up to weeks 12, 26, and 52. ANCOVA will be used as in the primary analysis to yield the mean difference between groups, adjusted for baseline costs and other important baseline covariates that are identified.

A cost-effectiveness analysis (CEA) comparing the two intervention groups using pain as the effectiveness measure will also be performed. Cost-effectiveness will be evaluated with the incremental cost-effectiveness ratio (ICER). The ICER is defined for this study as the adjusted mean difference between groups in costs divided by the adjusted mean difference in patient-rated pain. ICER will be calculated at the same time points used in the primary analysis.

A cost-utility analysis (CUA) will be performed to compare the intervention and control groups using the EuroQol-5D. Utility will replace pain in the ICER.

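### Pain at week 12 and pain at week 52 are both primary and share one alpha of .05, with no split, order or rule on which of them decides the primary aim

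*Protocol article*

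**What the plan says.** The Primary Aim section of the protocol article asks for the relative efficacy of the two care models "in both the short-term (after 12 weeks) and long-term (after 52 weeks). Patient-rated back pain is the primary outcome measure". The Abstract frames the aim the same way.

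Under Data Analysis, Treatment Effectiveness, power is calculated for a difference of 8 to 9 percentage points "in the primary outcome measure of patient self-reported pain after 12 weeks and one year". The next sentence reads: "A sample size of 100 patients per group provides 80% power assuming an alpha level of .05". A 15% loss to follow-up is allowed for. Mixed-model ANCOVA is then used "to test for differences between groups in patient-rated primary and secondary outcomes in both the short- (12 weeks) and long-term (52 weeks".

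The Cost-effectiveness Analysis section also treats the primary analysis as having more than one time point: "ICER will be calculated at the same time points used in the primary analysis".

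The article does not rank the time points, divide the alpha between them, or say whether a difference at one time point is enough.

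**The concern.** One primary outcome is tested at two time points of equal standing, and only one alpha is stated. Read at face value, each test gets the full .05, so there are two opportunities for a primary claim. Whether the error of that claim is 5%, and whether the power is 80%, then depends on a decision rule that the article does not give.

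This matters most for a split result. Treatment lasts 12 weeks and follow-up 52, so a difference that is present at week 12 and gone by week 52, or the reverse, is quite possible. With no rule, whether such a result meets the primary aim could be settled after the data are seen.

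**Working it through.** **Inputs from the article.** Alpha .05 and power 80%; 100 randomized per group, 1:1; 15% loss; a difference of 8 to 9 percentage points, read as 0.8 to 0.9 on the 0-10 pain scale.

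**Assumptions, not in the article.** Two-sided tests; a normal approximation; a correlation ρ between the week-12 and week-52 test statistics, varied from 0 to 0.9; an SD, which has to be solved for.

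**1. The plan's own figure.** Evaluable per group: 100 × (1 − 0.15) = 85. With n = 2·SD²·(z₀.₉₇₅ + z₀.₈₀)²/Δ², the implied SD is Δ / [(1.960 + 0.842) × √(2/85)]. This gives 1.86 for Δ = 0.8 and 2.09 for Δ = 0.9. The stated sample size is therefore consistent with one test at the full .05 per time point. It does not prove that reading, because the SD was solved to fit. At .025 per test the same 85 per group would fit SDs of about 1.69 to 1.90.

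**2. Error if either time point counts, each at two-sided .05.** P(|Z₁| > 1.96 or |Z₂| > 1.96), with Z₁ and Z₂ bivariate normal under no difference at either time. At ρ = 0 this is 1 − 0.95² = 0.0975.

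**3. Error if both must be significant.** With no difference at either time, P(both) = 0.05 + 0.05 − P(either). If there is a real difference at one time only, the error can approach .05 but cannot exceed it.

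**4. Joint power if both must be significant.** With 80% power at each time, this is P(Z₁ < 0.842 and Z₂ < 0.842) with correlation ρ, ignoring the negligible opposite tail. At ρ = 0 it is 0.80² = 0.64.

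| ρ | Error, either counts | Error, both required (no difference at either time) | Joint power, both required |
|---|---|---|---|
| 0 | 9.75% | 0.25% | 64.0% |
| 0.3 | 9.5% | 0.5% | 66.6% |
| 0.5 | 9.1% | 0.9% | 68.7% |
| 0.7 | 8.35% | 1.65% | 71.3% |
| 0.9 | 7.0% | 3.0% | 75.0% |

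**5. Effect of .025 at each time point.**
- Error if either counts: 4.9% at ρ = 0 and 4.65% at ρ = 0.5.
- Power per time point at the design difference: Φ(2.802 − 2.241) = Φ(0.560) = 71%.
- Ratio of detectable differences at 80% power: (2.241 + 0.842)/(1.960 + 0.842) = 1.10. So 8 becomes 8 × 1.10 = 8.8 points and 9 becomes 9 × 1.10 = 9.9 points.
- Keeping 80% at the original difference would need 85 × 1.10² ≈ 103 evaluable, or 103/0.85 ≈ 122 randomized per group.

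**The case against.** The strongest reply is that this is silence in a condensed article. Ordering and multiplicity rules often sit in the full protocol or analysis plan, and neither is shown. That stands as far as it goes: a reader might infer that no adjustment will be made, but the article says only that it assumes an alpha of .05, once, and does not address adjustment.

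A reader might also infer that the false-positive rate is about 9% as a matter of fact. The article does not support that. The figure needs an either-counts rule, the full two-sided .05 at each test, and a correlation near 0.5, none of which is given. Nor does the article claim a familywise rate of 5% or a joint power of 80%.

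It can further be argued that short-term and long-term efficacy are two questions, each entitled to its own error rate, with both results reported. That position is defensible. But the article states them as one primary aim with one alpha, so it should say which view it takes.

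Finally, it would be tempting to make week 12 the gatekeeper. No section ranks week 12 above week 52, and that order would bar a confirmatory long-term conclusion after a null short-term result. The choice belongs to the sponsor.

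What survives is that the article itself fixes two primary time points, one alpha and one power figure. Under a both-required rule, or an alpha split at the SD implied in step 1, 80% would not be the power delivered. Under either-counts at full alpha, .05 would not be the error of the primary claim.

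**Conclusion.** The point holds in conditional form. Two primary time points share one stated alpha of .05 and one 80% power figure, without a decision rule. If either counts at two-sided .05, the chance of a false primary claim is about 7% to 9.75% across correlations from 0.9 to 0. If both are required, the error stays within 5%, but joint power is about 64% to 75%. A fixed order or a single deciding time point would keep both the error and the stated power for the first test.

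These ranges rest on two-sided tests, 80% marginal power at each time point and an assumed correlation. A rule may already exist in the unseen analysis plan. Severity: should-fix.

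**What to change.** Before any outcome analysis, state how the two time points are combined into the primary conclusion. Any one of these suffices:

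- **Control the error over both.** Use Holm or Hochberg across week 12 and week 52. The simpler alternative is .025 each, with the detectable difference at 80% power restated as about 8.8 to 9.9 percentage points.
- **Name one deciding time point, or a fixed testing order.** The sponsor chooses which comes first and gives the reason. The first test keeps alpha .05 and the stated 80% power.
- **Require both.** Alpha .05 per test is then adequate, but the joint power should be stated in place of 80%.

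If the full analysis plan already contains such a rule, cite it and bring the Treatment Effectiveness power statement into line.

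The cost is a sentence or two and no added patients, which matters because recruitment is already complete. The downside is a detectable difference about 10% larger under a .025 split (10% at most under Holm or Hochberg), or one time point's confirmatory claim becoming conditional on the other or secondary to it.

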### Cost-effectiveness Analysis

A cost comparison of the intervention groups using data on direct and indirect costs will be conducted. Cost differences between groups will be estimated for all costs up to weeks 12, 26, and 52. ANCOVA will be used as in the primary analysis to yield the mean difference between groups, adjusted for baseline costs and other important baseline covariates that are identified.

A cost-effectiveness analysis (CEA) comparing the two intervention groups using pain as the effectiveness measure will also be performed. Cost-effectiveness will be evaluated with the incremental cost-effectiveness ratio (ICER). The ICER is defined for this study as the adjusted mean difference between groups in costs divided by the adjusted mean difference in patient-rated pain. ICER will be calculated at the same time points used in the primary analysis.

A cost-utility analysis (CUA) will be performed to compare the intervention and control groups using the EuroQol-5D. Utility will replace pain in the ICER.

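### As written, the cost-utility ratio divides cumulative cost by the EQ-5D difference at one visit, so it is not a cost per QALY

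*Protocol article*

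**What the plan says.** All the defining text is in the protocol article, under Cost-effectiveness Analysis.

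- Costs are cumulative: "Cost differences between groups will be estimated for all costs up to weeks 12, 26, and 52".
- The ratio is given a formal definition: "The ICER is defined for this study as the adjusted mean difference between groups in costs divided by the adjusted mean difference in patient-rated pain".
- Timing: "ICER will be calculated at the same time points used in the primary analysis". Under Treatment Effectiveness, those time points are weeks 12 and 52.
- Cost-utility: "A cost-utility analysis (CUA) will be performed to compare the intervention and control groups using the EuroQol-5D", followed by "Utility will replace pain in the ICER".

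Under Self-report outcome measures, pain is the typical level over the past week on an 11-box scale ("0 = no LBP, 10 = the worst LBP possible"). It is therefore a level at a visit. The article nowhere mentions QALYs, area under the curve or any time weighting of utility.

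**The concern.** A utility score is a weight on time lived in a health state. To set it against costs that have built up over 12 or 52 weeks, it has to be accumulated over those same weeks, which gives QALYs. The article instead states a formula with a point-in-time score in the denominator and tells the analyst to swap one score for another. Carried out literally, that divides a quantity accumulated over a period by a level at the end of the period.

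The result could not be compared with a cost-per-QALY figure from elsewhere. At week 12 it would treat a utility difference as if it had lasted a full year. At week 52 it would ignore whatever happened between the arms earlier in the year. Study treatment stops at 12 weeks, so a difference that changes between weeks 12 and 52 is a realistic possibility. What is at stake is the reading of the cost-utility result.

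**Working it through.** **Inputs.** The article states no ICER, utility difference or QALY figure, so there is nothing of its own to reproduce. Visit times are baseline and weeks 4, 12, 26 and 52 (Abstract, Methods and Design), and utility measures are on those questionnaires (Figure 1 legend). The Cost-Effectiveness and Utility Measures section gives the same four numbers as months; I take weeks, since follow-up lasts one year. All utility trajectories and the $500 below are my assumptions.

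**Formulas.** Let d(t) be the between-group EQ-5D difference at week t.

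- Denominator as written at week T: d(T).
- QALY difference to week T: dQALY = (1/52) × sum over visit intervals of ½ × (d at start + d at end) × (weeks in interval).
- Factor = (cost / dQALY) ÷ (cost / d(T)) = d(T) / dQALY. The cost cancels. A factor above 1 means that the written ratio is too small by that multiple.

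**Week 12**

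| Assumed difference | d(12) | Area, utility-weeks | dQALY | Factor |
|---|---|---|---|---|
| 0.05 constant from day 0 | 0.05 | 0.05 × 12 = 0.60 | 0.0115 | 4.3 |
| 0.05 by week 4, held | 0.05 | 0.10 + 0.40 = 0.50 | 0.0096 | 5.2 |
| 0.04 at week 4, 0.06 at week 12 | 0.06 | 0.08 + 0.40 = 0.48 | 0.0092 | 6.5 |
| 0.025 at week 4, 0.05 at week 12 | 0.05 | 0.05 + 0.30 = 0.35 | 0.0067 | 7.4 |
| straight line from 0 to 0.05 | 0.05 | ½ × 0.05 × 12 = 0.30 | 0.0058 | 8.7 |
| 0 at week 4, 0.01 at week 12 | 0.01 | 0 + 0.04 = 0.04 | 0.0008 | 13 |

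The first row is simply 52/12. It needs a difference at baseline, which randomization and baseline adjustment should remove, so the rows from 5.2 upward are more realistic. The range describes the profiles tried and is not a bound: a difference that peaks at week 4 and then falls would give a smaller factor.

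**Week 52** (differences at weeks 4, 12, 26, 52; zero at baseline)

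| Assumed difference | Area, utility-weeks | dQALY | Factor |
|---|---|---|---|
| 0.05, 0.05, 0.05, 0.05 | 0.50 + 0.70 + 1.30 = 2.50 | 0.0481 | 1.04 |
| 0.025, 0.05, 0.05, 0.05 | 0.35 + 0.70 + 1.30 = 2.35 | 0.0452 | 1.11 |
| 0.04, 0.06, 0.03, 0.01 | 0.48 + 0.63 + 0.52 = 1.63 | 0.0313 | 0.32 |
| 0, 0.01, 0.03, 0.06 | 0.04 + 0.28 + 1.17 = 1.49 | 0.0287 | 2.1 |
| 0, 0, 0, 0.05 | 0.65 | 0.0125 | 4.0 |
| 0.05, 0.05, 0.05, 0 | 0.50 + 0.70 + 0.65 = 1.85 | 0.0356 | written ratio undefined |
| 0.04, 0.06, 0.03, 0 | 0.48 + 0.63 + 0.39 = 1.50 | 0.0288 | written ratio undefined |
| 0.05, 0.05, 0.01, -0.02 | 0.50 + 0.42 - 0.13 = 0.79 | 0.0152 | -1.3 (opposite sign) |

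A factor of 0.32 means that the written ratio is about three times too large (1/0.32 = 3.1).

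**Illustration.** Take a cost difference of $500 and 0.05 from week 4 onward. The written ratio is 500/0.05 = $10,000 at both time points. Cost per QALY is 500 × 52/0.50 = $52,000 at week 12 and 500 × 52/2.50 = $10,400 at week 52.

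**The case against.** The best defence is that this is a condensed article. The cost-utility analysis gets two sentences, and the way utility is accumulated is commonly left to a fuller plan that is not shown. Utility could be shorthand for QALYs, and the stated time points could be horizons, since the costs run up to them. The article also never promises a cost per QALY or names a threshold, so no labelled figure is wrong.

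Part of this stands: the fuller plan may well compute QALYs, and the article makes no false numerical claim. But the text is not silent. It gives a definition, "the adjusted mean difference between groups in costs divided by the adjusted mean difference in patient-rated pain", and a substitution rule, and nothing in it suggests accumulation. A rule that gives the wrong quantity when followed is worth correcting. It is also fair that the magnitudes rest on assumed trajectories, and that a QALY-based ratio can itself be undefined when the QALY difference is near zero. The specific fault is that the written ratio can be undefined or change sign when the QALY difference is clearly not zero.

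A reader might infer three further faults that the document does not support.

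- *The mention of a control group leaves the sign of the ratio open.* Both arms are active, so the wording is loose, but swapping the arms reverses numerator and denominator together: (-ΔC)/(-ΔU) = ΔC/ΔU. The ratio is unchanged.
- *The pain ratio has a misleading sign because higher pain is worse.* On the article's own coding, a dearer and better arm gives a negative ratio, and a cheaper and better arm a positive one. The two are not confused unless a benefit-coded convention is applied. Any ICER needs its quadrant reported, so this is a reporting convention.
- *The confidence interval for the pain ratio would often be unbounded.* That holds for any ratio with a non-significant denominator, including one based on QALYs. The article does not prescribe such an interval, and it states no standard deviation from which to work out how often this would happen.

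**Conclusion.** The point holds for the utility denominator. Followed literally, the article divides cumulative cost by a point-in-time EQ-5D difference. At week 12 the ratio is about 4 to 13 times smaller than the cost per QALY under the trajectories tried, chiefly because 12 weeks is only 0.23 of a year. At week 52 the outcome depends on the course of the difference. It is close to right if sustained, and off by roughly 2- to 4-fold in either direction, undefined or of opposite sign if the difference comes late, fades or reverses.

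It would go too far to say that the trial's economic conclusion will be wrong, or that the dearer arm is bound to be favoured at week 12. The first depends on trajectories that the document does not give. The second also requires the dearer arm to have the better utility, which is unknown. The matter is confined to the cost-utility analysis, which is listed under neither the Primary Aim nor the Secondary Aims heading, although the Abstract says that cost utility will be assessed. The primary pain analysis is not touched.

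**What to change.** Replace the substitution sentence with wording such as: *For the cost-utility analysis, the denominator is the between-group difference in QALYs, computed as the area under each participant's EQ-5D utility curve (baseline and weeks 4, 12, 26 and 52) over the same period as the costs, and adjusted for baseline utility.* The 12-week ratio would use the baseline, week-4 and week-12 scores; the 52-week ratio would use all five.

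The cost is wording only. The EQ-5D is already on the planned questionnaires at those visits, and no new data, visits or participants are needed. If the fuller plan already defines QALYs in this way, the article's sentence needs only to be brought into line with it.
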